### Study procedure

#### Staff training

Personnel who participate directly in this study will be adequately trained to ensure the safety of the patients, blinding of the study design, data quality, and adherence to the study protocol. Personnel follow guidelines for good clinical practice (GCP).

#### Recruitment, screening, and enrollment

We will follow criteria to recruit, screen, enroll and reject patients. Patients will be enrolled if they conform to all inclusion criteria. However, they will not be enrolled if they have one of the exclusion criteria, rejection criteria, or termination standards. Furthermore, it is the responsibility of participant to cooperate with the doctor’s treatment. Additionally, they should cooperate with our follow-up and provide us with information that is not beyond the ethical approval.

#### Inclusion and exclusion criteria

Inclusion criteria are patients (i) with confirmed infection by the influenza A (H1N1, H3N2) or influenza B virus according to real-time polymerase chain reaction (PCR) or viral culture; (ii) aged 18 to 65 years; axillary temperature ≥38°C; at least two constitutional symptoms (headache, chill, myalgia or fatigue) and one respiratory symptom (cough, sore throat, or rhinitis) [30,31]; (iii) illness onset within 36 h; and (iv) granting of written informed consent. Exclusion criteria are detailed in Table 2.

**Table 2 Tab2:** **Inclusion and exclusion criteria**

**Inclusion criteria**	**Exclusion criteria**
(1) With confirmed infection by the influenza A (H1N1, H3N2) or influenza B virus according to real-time polymerase chain reaction (PCR) or viral culture	(1) Age <18 years or >65 years
	(2) Confirmed bronchitis, pneumonia, pleural effusion and interstitial lung disease *via* chest imaging (radiograph or CT)
(2) Aged 18 to 65 years; axillary temperature ≥38°C and at least two constitutional symptoms (headache, chill, myalgia or fatigue) and one respiratory symptom (cough, sore throat, or rhinitis)	(3) Routine screening tests of blood with leukocyte readings >10.0 × 10^9^/L or neutrophil count ≥80%
	(4) Suppurative tonsillitis or purulent sputum
(3) Illness onset within 36 h	(5) Underling primary disorders such as hematological disease, chronic obstructive pulmonary disease (FEV_1_/FVC <70%, FEV_1_/predicated value <50%; or respiratory failure or right-heart failure), hepatic disease (ALT or AST ≥ triple ULN), renal disease (serum creatinine > 2 mg/dL) or chronic congestive heart failure (NYHA III to IV)
(4) Granting of written informed consent	
	(6) Previous administration of antiviral drugs (amantadine, rimantadine, zanamivir, or oseltamivir phosphate) before disease onset and study enrollment, or administration of traditional Chinese herbal medicine or proprietary Chinese medicine. Administration of BLG granules within 1 week before disease onset
	(7) Allergy to study medication(s)
	(8) Women who are pregnant, or may possibly become pregnant, or who are lactating with a positive urine pregnant test, or with a body mass index (BMI) ≥25 kg/m^2^
	(9) The immunodeficient: malignant tumor; organ or bone-marrow transplantation; AIDS; or taken immune inhibitors during the last 3 months
	(10) Suspicion or history of alcohol/drug abuse
	(11) Participation in another clinical trial <3 months before study randomization
	(12) Acute respiratory infection, otitis, or nasosinusitis 2 weeks before study enrollment
	(13) Vaccination with the influenza vaccine within 6 months
	(14) Other reasons at the investigator’s discretion

#### Rejection criteria and termination standards

Rejection criteria were (i) not meeting inclusion or exclusion criteria; (ii) withdrawal of informed consent; (iii) not receiving follow-up care after selection; or (iv) serious violation of the program (that is, incorrect administration leading to effects that cannot be judged).

Termination standards refer to patients who meet the inclusion criteria, but must be terminated during the trail and who are included in the final statistical analyses. Termination standards are detailed in Table 3.

**Table 3 Tab3:** **Termination standards**

**Criteria**	
1	The patient’s illness becomes severe, and the severity meets one of the following criteria: (i) persistent high fever for >3 days (≥39°C); (ii) Severe cough, purulent sputum, bloody sputum, or pectoralgia; (iii) rapid breathing, trouble in breathing, lip cyanosis; (iv) alternation of consciousness (that is, drowsiness, restlessness, convulsions); (v) severe vomiting, diarrhea, dehydration; (vi) imaging confirms signs of pneumonia; (vii) levels of myocardial enzymes, such as creatine kinase (CK), creatine kinase isoenzyme (CK-MB) elevate rapidly; (viii) underlying diseases are exacerbated significantly.
2	Death (including deaths due to influenza and other causes of death)
3	Antibiotic treatment is required (bacterial pneumonia, tympanitis, nasosinusitis secondary to influenza)
4	Serious events occur
5	Other health reasons

### Drugs and usage

#### Oseltamivir treatment group

The oseltamivir treatment group will receive one oseltamivir capsule, (75 mg/per capsule), twice a day [29], 30 minutes after eating, taken with two bags of analogous BLG granules.

#### Ban-Lan-Gen *treatment group*

The BLG group will receive two bags of BLG granules (10 g/per bag), twice a day (the dosage is set according to the regulations of the China Food and Drug administration*.*), 30 minutes after eating, taken with an analogous oseltamivir capsule.

#### Placebo group

The placebo group will receive BLG analogous granules, twice a day, 30 min after eating, taken with an analogous oseltamivir phosphate capsule.

The BLG granules and the BLG analogous granules were produced according to the quality requirements of the *People’s Republic of China Pharmacopoeia* (Additional files 1 and 2)*.* Furthermore, the placebo includes white powdered sugar (41.1%), brown powdered sugar (22.6%), amylum (16.43%), dextrin (10.27%), caramel syrup (1.4%), and lemon yellow (8.2%).

All drugs were packaged by Hutchisom Whampoa Guangzhou Baiyunshan Chinese Medicine Company Limited (Guangzhou, China) according to the requirements of a double-blind, double-simulation test. The drugs used in this double-blinded trial were counted and sorted by a third party (Southern Medical University, China). All drugs were in the period of validity.

Other treatments for participants have to meet the standards for using other drugs, which are axillary temperature ≥38.5°C that continues more than 4 hours and does not degrade with physical cooling or body temperature is gradually raised ≥ 39°C. When these standards are met, the symptoms are treated as indicated: fever: paracetamol; white sputum, bromhexine; and mild asthmatic symptoms, long-term theophylline. With these exceptions, no other drugs can be used. Furthermore, detailed information on the drug use will be registered in the case report form (CRF).

### Outcome measurements

Drug efficacy was determined using patient symptoms, body temperature, and virus detection.

#### Primary outcome

The first primary outcome is the duration of the illness and will be measured in hours. Duration of illness is defined as the time from symptom onset to alleviation of the influenza-like symptoms: nasal obstruction, running nose, cough, sore throat, headache, fatigue, myalgia, chills and sweating. The definition of symptom alleviation is influenza-like symptoms score ≤1 (mild) and maintenance of stable symptoms for more than 24 h [30,32].

Another primary outcome is the time to defervescence, which is measured in hours. The time from the first dose of the study medication to the time when the body temperature decreases to <37.4°C is defined as ‘defervescence,’ and when it is sustained for ≥24 h, it is defined as ‘complete defervescence’ [30,32].

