### Design

This clinical study was a randomized, double-blind, double control trial that tested drugs and placebo. Noninferiority (versus positive control) and superiority (versus placebo control) trials were conducted. Patients with positive tests for the influenza virus (rapid detection of antigens to the influenza virus before enrollment, but if detection of nucleic acid of the influenza virus or cultivation of the influenza virus was inconsistent, the patient was excluded) were assigned randomly into three groups of equal proportions (1:1:1). Groups were: oseltamivir treatment (positive control), BLG granule treatment (test group) and placebo group. Patients will accept 5-day treatment and 21-day observation. Patient follow-up was undertaken on days 1, 3, 5, 7, 21 (Table 1 and Figure 1). Specific items that were collected for each follow-up period are outlined in Table 1.

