**Table 1 Tab1:** **Follow-up chart of treatment using ban-lan-gen granules against seasonal influenza**

**Visit cycle evaluation projects**	**Screening stage**	**Remedial period**			
	**Visit 0 day 0.5 to 0**	**Visit 1 Day 3 + 1 after administration**	**Visit 2 Day 5 + 1 after administration**	**Visit 3 Day 7 + 1 after administration**	**Visit 4 Day 21 + 7 after administration**
Acquisition of basic medical history					
Informed consent	X				
Basic conditions	X				
Symptoms	X	X	X	X	
Inclusion and exclusion criteria	X				
Safety observations					
Vital signs	X			X	
Electrocardiography	X	a	a	X	
Chest radiograph	X	a	a	a	
Laboratory inspection	X	a	a	X	
Record adverse events	X	X	X	X	X
Efficacy					
Record influenza symptoms	X	X	X	X	
Virology					
Rapid diagnostic tests	X				
Real-time PCR analyses	X	X	X	X	
Viral isolation culture	X	X	X	X	
Viral antibody titer	X				X
Other					
Grouping and giving drugs	X				
Administer drugs	X	X	X		
Distribute patient diary card	X				
Accompanying treatment	A	A	a	a	
Compliance	X	X	X	X	
Inspection results	X				X
Original record completion	X	X	X	X	X
Recover study drug				X	
Recover patient diaries				X	
CRF review, recovering and test summary					X

X, must implement; a, necessary to implement.

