### Number of participants and specimen collection

Recommendations from the World Health Organization for influenza-like illnesses (ILIs) were used as the basis for influenza surveillance. If a patient presents with an acute cough and fever, clinicians must be highly vigilant to test for infections caused by the influenza virus. In general, the rate of ILI cases that lead to a clinical diagnosis of influenza infection is approximately 18 to 80%, which is higher than other clinical diagnoses, for example, acute infections of the upper respiratory tract [28]. We selected adult ILI patients for inclusion into the study. The study was designed to enroll 177 cases.

Specimen collection included pharyngeal/throat swabs and blood samples. Pharyngeal/throat secretions were obtained from the upper respiratory tract of each patient [29]. Pharyngeal/throat swabs will be used to test the mRNA of the influenza virus; the virus will be cultured. Blood samples will be used to test viral antibodies.

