#### Secondary outcome

Five secondary endpoints are being considered. The first is the duration of viral shedding. This endpoint is defined as the time from illness onset to the first time the viral nucleic acid test is negative. The second endpoint is disease severity. It is assessed by an area under the curve (AUC) analysis of nine influenza-like symptom scores [29]. The AUC is calculated as the product of the daily symptom scores multiplied by the duration of illness. The third endpoint is the frequency of acetaminophen usage. The fourth endpoint is the prevalence of secondary influenza complications. These are otitis, bronchitis, pneumonia, nasosinusitis, suppurative tonsillitis, acute parotitis, Reye’s syndrome, central nervous system disease, myocarditis, pericarditis, acute myositis, and toxic shock syndrome. The final endpoint was an economic evaluation.

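### The two primary outcomes start their clocks at different points; the onset clock for illness duration adds untreatable pre-dose time, a small noise cost that a delay covariate would remove

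*Protocol article*

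**What the plan says.** All references are to the protocol article.

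- **Primary outcome**, first outcome: "Duration of illness is defined as the time from symptom onset to alleviation of the influenza-like symptoms". It is measured in hours.
- **Primary outcome**, second outcome, also in hours: "The time from the first dose of the study medication to the time when the body temperature decreases to <37.4°C".
- **Secondary outcome**, viral shedding: "the time from illness onset to the first time the viral nucleic acid test is negative".
- **Inclusion and exclusion criteria**: "illness onset within 36 h". The limit is a condition of entry and is not tied to the time of first dose. Table 1 gives the screening window as "Visit 0 day 0.5 to 0".
- **Design**: "Noninferiority (versus positive control) and superiority (versus placebo control) trials were conducted", with equal allocation to three arms.
- **Statistical analyses**: quantitative efficacy variables are compared by repeated-measures ANOVA and ANCOVA, two-sided at 0.05. That is a comparison of means. The article names no covariates.

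No reason is given for using two different origins.

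**The concern.** Illness duration in this trial is the sum of two parts: the time from onset to first dose, which is settled before study drug can act, and the time from first dose to alleviation, which treatment may shorten. Only the second part carries information about the drug. The first part is a patient characteristic. Onset precedes any trial observation, so its time presumably comes from the patient's history, although the article does not say how it is obtained.

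If the first part varies between patients and is unrelated to the second, it adds variance to one primary outcome and to viral shedding. The second primary outcome does not carry this component. At stake is a modest loss of precision, in both the comparison with placebo and the comparison with oseltamivir, that can be avoided with data the trial already needs.

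**Working it through.** **Inputs from the article.** "The study was designed to enroll 177 cases", allocated 1:1:1, so 177 / 3 = 59 per arm. Test two-sided at 0.05. Onset at most 36 h before entry. The article gives no SD, effect size or power, so the total of 177 cannot be rebuilt from it.

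**Assumptions.** Delay W from onset to first dose is uniform on 0 to 36 h. Post-dose duration P has an SD of 30, 48, 72 or 96 h. The true difference is 24 h. At first, W is taken as independent of P. The onset-based duration is O = P + W.

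**Step 1: expected difference.** E(O | arm) = E(P | arm) + E(W), and E(W) is the same in every randomised arm, so it cancels. Example: 110 vs 85 h from first dose is a 25 h difference. With a mean delay of 18 h it becomes 128 vs 103 h, still 25 h.

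**Step 2: variance.** Var(W) = 36²/12 = 108 h², so SD(W) = 10.4 h. Variance ratio, onset clock to dose clock = 1 + 108/SD².

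**Step 3: power.** Power = Φ(24 / (SD × √(2/59)) − 1.96), with SD replaced by √(SD² + 108) for the onset clock.

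| Post-dose SD (h) | SD, onset clock (h) | Variance ratio | Power, dose clock | Power, onset clock | Loss (points) |
|---|---|---|---|---|---|
| 30 | 31.7 | 1.12 | 99.1% | 98.4% | 0.7 |
| 48 | 49.1 | 1.05 | 77.5% | 75.6% | 1.9 |
| 72 | 72.7 | 1.02 | 44.1% | 43.3% | 0.8 |
| 96 | 96.6 | 1.01 | 27.4% | 27.1% | 0.3 |

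In patients per arm, 59 / 1.12 = 52.7 at SD 30 h (about 6 lost) and 59 / 1.05 = 56.2 at SD 48 h (about 3 lost).

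The 36 h limit applies to entry. If dosing could follow by up to a further 12 h (one reading of the half-day screening window, taken as uniform and independent), Var(W) = 108 + 12²/12 = 120 h². The increase at SD 30 h is then 120/900 = 13% instead of 12%, so the conclusion does not depend on this.

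**Step 4: dropping independence.** A simulation used 59 per arm, 1,500 runs per scenario, log-normal durations and a treated-to-control time ratio of 0.75 after dosing. The standard error of each power is at most √(0.25/1500) = 1.3 points; both clocks were applied to the same simulated patients.

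- Delay independent of post-dose time: log-rank power fell by at most 2.3 points (95.7% to 93.4% at sigma 0.4). Hazard ratios barely moved: 1.94 to 1.89, 1.53 to 1.53 and 1.41 to 1.40 at sigma 0.4, 0.6 and 0.8.
- Total illness length independent of delay, so that later presenters have less illness left: t-test power was 86.5% by the dose clock and 88.1% by the onset clock at sigma 0.4, and within 0.5 points of each other at sigma 0.6 and 0.8.

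**Step 5: effect of a covariate.** Suppose P is modelled as a + b × arm + c × W. Then O = P + W gives a + b × arm + (c + 1) × W. The treatment coefficient b and the residuals are identical under either clock. This holds whatever the value of c, that is, however delay relates to recovery.

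**The case against.** The strongest case against is that this is a design preference and not an error. The two outcomes are separate and explicitly defined, they are never combined, and total illness duration means something to patients. ANCOVA is already planned, and its covariates are commonly left to an analysis plan, which is not shown here. The trial was registered and 50 patients had finished by June 2014, so redefining a primary outcome is more than a wording change. All of this stands. What it does not remove is the avoidable noise.

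A reader might infer four stronger things that the article does not support.

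- *The onset clock dilutes the treatment effect.* This is true only of a percentage or ratio of times. For 110 vs 85 h the ratio moves from 85/110 = 0.77 to 103/128 = 0.80. For 120 vs 90 h, a 25.0% reduction becomes 21.7% with 18 h added and 19.2% with 36 h added. No such measure is planned, and Step 1 shows no change in hours.
- *It makes BLG look closer to oseltamivir and so eases non-inferiority.* This needs the same unplanned ratio. On the mean-difference scale the expected gap is unchanged, and extra variance widens the interval, which makes a fixed margin harder to meet.
- *Chance imbalance in delay is a further problem.* The 95% range for the difference in mean delay between two arms is ±1.96 × 10.4 × √(2/59), or about ±3.7 h. This is the same variance as in Step 2 in another form, already inside the confidence interval.
- *No event can occur before entry, so the comparison is biased.* That selection applies equally to all randomised arms and does not bias the difference in means.

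**Conclusion.** The point holds as a modest inefficiency. The two primary outcomes have different origins, and illness duration and viral shedding carry a pre-treatment interval of roughly 0 to 36 h that treatment cannot affect. The between-arm difference in hours remains unbiased. With a uniform delay independent of post-dose duration and a post-dose SD of 30 to 96 h, the variance of illness duration is about 1 to 12% higher, costing about 0.3 to 2 power points at a 24 h difference. The upper figure of 12% needs the smallest SD considered. If later presenters have less illness left, the cost can disappear or turn slightly in favour of the onset clock. The delay distribution, the SDs, the 24 h difference and independence are all assumptions, since the article gives none of them. The case for acting rests on how little the remedy costs, not on the size of the harm.

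**What to change.** 1. Prespecify onset-to-first-dose time as a baseline covariate in the covariance analysis of illness duration and viral shedding. On the hours scale this gives the same treatment estimate under either clock and takes out the part of the variance due to delay. Onset time is needed for eligibility and first-dose time for defervescence, so no new data are required. First dose comes after allocation, but the trial is double-blind and Table 1 places allocation and the start of dosing at the same visit, so the arm should not influence the delay. The exact equivalence is a property of the linear model; it would not carry over unchanged to a log-transformed or Cox analysis.

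2. Preferably, also report illness duration and viral shedding from first dose, in line with defervescence, and keep the onset-based durations as descriptive.

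Step 1 costs one sentence in the analysis plan. If step 2 changes the definition of the primary outcome, it needs an amendment with a stated reason before unblinding, which the Data management section places after database lock. The other cost is slightly less direct comparison with studies that report duration from onset.

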#### Statistical analyses

The software used for statistical analyses will be SPSS v17.0 (IBM, Armonk, NY, USA) or SAS v9.2 (SAS Institute, Cary, NC, USA).

All statistical inferences will be determined using two-sided tests. *P* <0.05 will be considered significant, and 95% confidence intervals will be used.

Efficacy analyses will use LOCF to compensate for cases not fully covered during treatment. The LOCF approach uses the last data observed, which is transferred to the database to obtain a complete dataset. The safety assessment will not evaluate missing data.

A comparison between the dropout rate and dropout rate caused by adverse events will be undertaken using the Pearson’s χ^2^test.

Data will be described as the mean, standard deviation, and confidence intervals. If necessary, minimum, maximum, P25, P75, and median values will be provided. Paired measurement data will also show the differences between the mean and standard deviation. When using nonparametric methods, median and mean values will be provided. Count data will be described using the frequency distribution and corresponding percentage. Data of concentrations will be described using the frequency distribution and the corresponding percentage, as well as median and average values. Qualitative information will be described using the positive rate, the number of positive cases, and the denominator.

Baseline data analyses (two sets) will include demographic indicators, as well as general, primary and secondary indicators before intervention. Measurement data will be described using a *t*-test or t’ test (if the variance is absent). Count data will be described using the Pearson’s χ^2^test. Rating data will be described using the two-sample Wilcoxon rank sum test.

With respect to analyses of effectiveness, for quantitative variables, comparisons between groups will be undertaken using repeated measures analysis of variance and covariance analysis. For qualitative variables, comparisons between groups will be tested using the Pearson’s χ^2^test, whereas center effect analysis will use CMH. For rating variables, comparisons between groups will be tested using the Kruskal-Wallis test, regression analysis center effect via the CMH test, or grade logistics.

In terms of center effect analyses, the GLM method will be used for quantitative indicators and CMH methods for qualitative indicators. Rating variables will be evaluated and corrected using a logistic regression model.

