With regard to subgroup analyses, depending on the circumstances, factors that cannot be excluded may have an effect on the prognosis.

For safety analyses, the prevalence of adverse events in the two groups will be compared using the Pearson’s χ^2^test, as well as listing and describing the events that occur during the trial. A description of laboratory test results before and after the test will be described as normal/abnormal changes, as well as the relationship between the abnormal changes and the test drug; these changes will be stated.

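### Two primary outcomes and two objectives share a flat two-sided P<0.05 with no rule on which must succeed, and the efficacy tests are not tied to the BLG contrasts

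*Protocol article*

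**What the plan says.** Under Primary outcome, the protocol article states: "The first primary outcome is the duration of the illness and will be measured in hours". The next paragraph adds: "Another primary outcome is the time to defervescence, which is measured in hours". Under Design it sets two formal objectives: "Noninferiority (versus positive control) and superiority (versus placebo control) trials were conducted". Patients are randomized 1:1:1 to three arms, and the planned total is 177.

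Under Statistical analyses one rule covers everything: "All statistical inferences will be determined using two-sided tests", with P below 0.05 counted as significant and 95% confidence intervals. For quantitative variables, groups are to be compared by repeated measures ANOVA and ANCOVA. Both primary outcomes are measured in hours, so this is the sentence that applies to them. It names no pair of arms. For ordinal data the text says: "For rating variables, comparisons between groups will be tested using the Kruskal-Wallis test".

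Two other places read as if there were two arms. Baseline rating data are to be handled by a two-sample Wilcoxon test, and for safety "the prevalence of adverse events in the two groups will be compared using" a Pearson chi-square test.

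**The concern.** Two outcomes and two objectives make four primary tests. Each is held to the same 5% level, and no order or joint success rule is stated. If illness duration fails and defervescence succeeds, the text does not say whether the trial has shown efficacy, so the answer could be chosen after the results are known.

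There is also a gap between the objectives and the tests. Both objectives are BLG contrasts, but the efficacy tests are described only as comparisons between groups. If that is taken as a global test over three arms, a significant P-value says that some arms differ, not that BLG differs from placebo. Oseltamivir is an active control, so a difference between oseltamivir and placebo alone could produce it. A global test of difference also cannot establish noninferiority, which needs a confidence limit for BLG versus oseltamivir set against a margin.

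**Working it through.** **Inputs from the article.** Two primary outcomes; two objectives; two-sided 0.05 for each inference; 177 patients in three equal arms, so 177/3 = 59 per arm. The article gives no derivation of 177, so there is no power figure to reproduce.

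**Assumptions.** The correlation r between the two outcomes' test statistics ranges from 0 to 0.9. The two comparisons share the BLG arm, which with equal arms gives a correlation of 0.5 between them. Test statistics are treated as multivariate normal.

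**Step 1: two outcomes within one comparison, either may succeed.** If independent:
- either direction: 1 − 0.95² = 0.0975
- in BLG's favour only: 1 − 0.975² = 0.0494, against a nominal 0.025

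**Step 2: all four tests.** If all four were fully independent, the two-sided rate would be 1 − 0.95⁴ = 0.185. Allowing for the shared BLG arm lowers this. Simulation with correlated outcomes gives:

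| r | Two tests, two-sided | Two tests, in BLG's favour | Four tests, two-sided | Four tests, in BLG's favour |
|---|---|---|---|---|
| 0 | 0.098 | 0.049 | 0.173 | 0.089 |
| 0.3 | 0.095 | 0.048 | 0.169 | 0.085 |
| 0.5 | 0.091 | 0.045 | 0.162 | 0.081 |
| 0.7 | 0.084 | 0.042 | 0.149 | 0.074 |
| 0.9 | 0.071 | 0.035 | 0.126 | 0.063 |

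Against the nominal 0.05, two tests give 1.4 to 1.95 times and four tests about 2.5 to 3.5 times. The four-test columns place all four null hypotheses on their boundary at once. With BLG equal to placebo, that happens only if the noninferiority margin equals the whole oseltamivir effect. These columns are therefore upper figures.

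**Step 3: both outcomes must succeed.** A false claim then needs two rejections, so the rate within a comparison cannot exceed that of a single test. There is no inflation.

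**Step 4: what a global test can show.** Take 59 per arm, BLG identical to placebo, and oseltamivir better by d standard deviations. The noncentrality of the F-test on (2, 174) degrees of freedom is 59 × (2/3) × d². The article gives no effect or SD; for illustration assume a 24 h oseltamivir effect:

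| Assumed SD | d | Noncentrality | Probability of P<0.05 |
|---|---|---|---|
| 80 h | 24/80 = 0.3 | 3.54 | 37% |
| 60 h | 24/60 = 0.4 | 6.29 | 60% |
| 40 h | 24/40 = 0.6 | 14.16 | 93% |

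In each row BLG has no effect. The calculation uses a one-way F-test on the durations as a simple stand-in for the repeated measures and covariance models that the article names.

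**The case against.** The strongest reply is that this is a condensed article, that the analysis plan is not shown, and that success rules and model contrasts are commonly placed there. This has force: the absence of an adjustment is not by itself the point. What remains is that the printed rule applies one level to all inferences, and that the printed efficacy tests are not linked to the printed objectives. Any rule held elsewhere would have to modify that text.

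A reader might draw several stronger conclusions that the documents do not support:

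- That a false efficacy claim against placebo would occur well above 5% of the time. The 9.75% counts both directions. In BLG's favour the rate is 3.5 to 4.9%: inflated over 2.5%, but below 5%.
- That the error rate simply doubles. This describes two weakly or moderately correlated outcomes in one comparison when either suffices. The article does not say that either suffices, and if both are required the inflation within a comparison is nil.
- That the primary outcomes are to be tested by Kruskal-Wallis or by two-group tests. Kruskal-Wallis is named for rating variables, and the two-group wording stands in the baseline and safety text. None of it concerns outcomes in hours.
- That a global test is certain to decide the claim. ANOVA and ANCOVA can produce pairwise contrasts, and the Design section implies which ones. The text leaves the choice open; it does not commit to the wrong one.

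The article also calls the trial a pilot with a larger trial to follow. That lowers the stakes but does not remove them, because formal noninferiority and superiority objectives are declared.

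**Conclusion.** The point holds as a needed clarification with a measurable consequence. Two primary outcomes and two objectives are judged at one flat level with no stated success rule. If either outcome may carry the claim, two-sided familywise error is about 7 to 9.75% within one comparison, and at most about 13 to 17% over four tests. In BLG's favour the rates are 3.5 to 4.9% and about 6 to 9%, each against a nominal 2.5%. These ranges rest on assumed outcome correlations of 0 to 0.9, and the four-test values also on all nulls being at their boundary.

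The efficacy tests are not tied to a BLG contrast. On the global reading, a significant result need not concern BLG and cannot show noninferiority. The 37 to 93% range illustrates how easily this could happen under assumed effects; it does not predict this trial.

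**What to change.** State that primary claims rest on the pairwise BLG contrasts implied by the Design section and not on a global three-arm test. Test them in fixed sequence, each at two-sided 5%, stopping at the first failure:

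1. BLG versus placebo, illness duration
2. BLG versus placebo, time to defervescence
3. BLG versus oseltamivir, noninferiority on illness duration
4. BLG versus oseltamivir, noninferiority on time to defervescence

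Report oseltamivir versus placebo as a check of assay sensitivity, outside the sequence. Putting illness duration first follows the article's own order; placing noninferiority after both placebo tests is a choice. Requiring both outcomes to succeed would also be valid within a comparison. The rule should be fixed and dated before unblinding.

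The cost is one paragraph, with no split of alpha and no extra patients. The downside is that defervescence supports a claim only if illness duration succeeds first, and noninferiority only after both. For comparison, a Bonferroni split over the two outcomes at 0.025 each multiplies the sample size by 1.21 at 80% power (63 to 77 per arm for an assumed 0.5 SD effect). With 59 per arm it cuts power for that effect from 77.5% to 68.2%.

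Separately, reword the safety comparison and the two-sample baseline tests for three arms, naming the pairs where pairs are meant.
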